### ***1.2 Title of the study***

Cross-sectional observational study to assess the prevalence of Covid-19 among those attending a music festival using the Public Health registries

### ***1.3 Code of the protocol***

SAFetival\_Salut

### ***1.6 Primary objective***

Prevalence of Covid-19 among those attending the Cruïlla festival and the CanetRock festival.

### ***1.7 Design***

This is a retrospective cohort study comparing the incidence of Covid-19 between individuals that attended the Cruïlla music festival and a control cohort that did not attend this event. It will also compare the incidence of Covid-19 between individuals that attended the CanetRock music festival and its corresponding control cohort that did not attend this event.

The attendees and the control cohort will be paired according to the following characteristics: age, gender, geographical area and COVID-19 immune status (vaccine/reinfection). The study will compare the number of individuals who tested positive for Covid-19 in each cohort, before and after the festival.

Briefly, data identifying Cruïlla festival attendees and CanetRock festival attendees will be transferred to the Catalan Health Authorities, who will collect information regarding their Covid-19 vaccination status from the Public Health registries. Each attendee will be paired to a control subject (based on age, gender, geographical area and Covid-19 immune status). Then, the number of positive SARS-CoV-2 tests between attendees and

controls on the 14 days after the festival will be compared. Data regarding positive SARS-Cov-2 tests after the festival of the attendees and the control group will be collected from the Catalan Health Department registry.

This data will be transferred anonymously (without any personal identificatory) to investigators from the Germans Trias i Pujol Hospital and Lluita contra la Sida Foundation to be interpreted.

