### ***1.10 Type of population and number subjects***

Study population will be subjects who underwent SARS-Cov-2 antigen test within the Cruïlla festival or the CanetRock Festival, and who are registered at the Catalan Public Health System. Overall, 40000 people underwent SARS-Cov-2 antigen test within the Cruïlla festival. For the CanetRock Festival, 22000 people underwent SARS-CoV-2 antigen test before attending the festival. The study will also include data from a control cohort, made of subjects that did not attend the event but were paired with the attendees. Pairing will be made 1:1 based on age, gender, geographical area and Covid-19 immune status (vaccine/previous infection).

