### 3 RATIONALE

The importance of the live events industry to the economy is significant. However, the public health response to COVID-19 led to an unprecedented closure in the entertainment industry. Although substantial advances have been made to re-open other industries, there has been limited experience on the reopening of live events such as live music concerts, festivals, or congresses. Because these experiences require people to be very close together, live events generally create conditions that favour virus transmission. Thus, preventive measures need to be adopted. However, there are no clear policy protocols to permit the return of live entertainment at full capacity.

Several self-care and risk mitigation strategies are currently being used.

On the one hand, facemasks wearing, handwashing, and capacity reduction to promote social distancing are non-pharmaceutical interventions available to reduce the basic reproduction rate of the virus.

Infection or immunity passports, which refer to tests that demonstrate negative infection status or immunity have also been used to re-open activities such as travelling.

Finally, given the continued roll out of vaccinations, vaccine passports have become a new criterion to demonstrate immunity in certain activities.

How to combine all these strategies in a cost-efficient manner to celebrate safely live events is still under debate.

On July 3, 2021, CanetRock music festival took place in Canet, a town located 40 km north-east of Barcelona, Catalonia, Spain. On July 8, 9 and 10, 2021, Cruïlla music festival took place in Barcelona, Catalonia, Spain. To reduce the risk of SARS-CoV-2 transmission within the festival, the organizers applied the following measures.

- Attendees to the festival were screened for SARS-CoV-2 infection with Antigen Rapid Diagnostic Test (Ag-RDT) via a nasopharyngeal swab.
- Non-contact body temperature screening was performed.
- Attendees were given a certified Filtering facepiece 2 (FFP2) mask. The use of the mask was compulsory whenever people were not eating/drinking.

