### ***6.4 Control group selection***

Prevalence of COVID-19 among those attending the Cruïlla festival or the CanetRock festival will be compared with the prevalence of COVID-19 in a control cohort. The control cohort will be created according to the characteristics of the attendees (gender, age, geographical area, and COVID-19 immune status).

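### Controls are barred only from their own festival, so CanetRock controls may have been exposed at Cruïlla during follow-up, and attendees of both festivals have no stated rule

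*Protocol*

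**What the plan says.** Protocol section 1.7 sets up two comparisons. Cruïlla attendees are compared with "a control cohort that did not attend this event", and CanetRock attendees with "its corresponding control cohort that did not attend this event". Section 1.10 describes the control cohort, again in the singular, as "made of subjects that did not attend the event but were paired with the attendees".

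Sections 6.1 and 6.4 say how controls are chosen, and name only the matching variables: sex, age, place and immune status. Neither section mentions attendance at the other festival. Sections 3, 6.1 and 8.1 treat the festivals as two parallel, independent comparisons, and no section says how a person who went to both is handled.

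The dates are in section 3: "On July 3, 2021, CanetRock music festival took place in Canet", about 40 km from Barcelona, and "On July 8, 9 and 10, 2021, Cruïlla music festival took place in Barcelona". The primary endpoint in section 7.1 counts any positive SARS-CoV-2 test in the 14 days following the festival, whatever the source of infection.

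**The concern.** The study is meant to show whether attending a screened festival was followed by more infections than not attending. That contrast needs controls who were not exposed to a comparable event in the same risk period. Each control cohort is defined only against its own event, and the two events were 5 to 7 days apart in the same part of Catalonia. Matching on age and area draws controls from the same local strata as the attendees, so a CanetRock control could have been at Cruïlla in the middle of follow-up.

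Two effects are at stake. Exposed controls raise the control frequency and make attendees and controls look more alike. CanetRock attendees who went on to Cruïlla carry a second exposure inside the CanetRock follow-up, and infections from it are counted in the CanetRock attendee frequency. Section 3 says the results should inform on how well the preventive measures worked, so either effect bears on the main message.

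**Working it through.** **1. The plan's own period.** Section 6.2 takes 14 days on each side of the festival and prints 24 June to 24 July. For Cruïlla, 8 July − 14 days = 24 June and 10 July + 14 days = 24 July, so the printed period reproduces. For CanetRock, 3 July ± 14 days gives 19 June to 17 July. The printed start therefore does not fit CanetRock's period before the event; that is a separate matter and does not affect what follows.

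**2. Follow-up windows.**
- CanetRock: 4–17 July.
- Cruïlla, counted from its last day: 11–24 July (9–22 July for someone attending only on 8 July).
- Cruïlla's three days fall 5, 6 and 7 days after CanetRock, all inside CanetRock's follow-up.
- CanetRock (3 July) falls before Cruïlla's follow-up, inside its period before the event (from 24 June).
- The two follow-ups share 11–17 July, 7 of 14 days (9–17 July, 9 days, if counted from 8 July).

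**3. The two directions are not alike.** The additional analysis in section 7.1 sets aside positives within 2 days of attendance and positives 6 days after the last day. That leaves days 3–5, or 3–6 if day 6 is kept. By this yardstick:
- infections acquired at CanetRock surface on 6–8 (or 6–9) July, before 11 July;
- infections acquired at Cruïlla surface on 11–15 (or 11–16) July, wholly inside CanetRock's follow-up, which ends on 17 July.

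Cruïlla can thus contaminate CanetRock's primary endpoint directly. CanetRock reaches Cruïlla's endpoint only through infections detected late.

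**4. Exposed controls.** Let p be the risk of an unexposed control, r the risk ratio of attendance, and c the share of controls who attended the other festival and carry the same r. Attendee risk is pr. Control risk is p(1 − c) + prc = p(1 + c(r − 1)). The observed ratio is r / (1 + c(r − 1)).

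| True r | c = 3% | c = 10% |
|---|---|---|
| 2 | 2/1.03 = 1.94 | 2/1.10 = 1.82 |
| 3 | 3/1.06 = 2.83 | 3/1.20 = 2.50 |

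Neither r nor c is in the documents. To judge a range for c, suppose controls are drawn at random from a matched pool of 250,000 to 2,000,000 people (assumed) that contains everyone screened at the other festival. With 40,000 screened at Cruïlla (section 6.5), c for CanetRock controls is 40,000/250,000 = 16% down to 40,000/2,000,000 = 2%. With 22,000 screened at CanetRock, c for Cruïlla controls is 8.8% down to 1.1%.

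**5. Dual attendees, CanetRock comparison.** If a share d of CanetRock attendees also went to Cruïlla, and the second exposure adds at most the same excess again, the observed ratio is (r + d(r − 1)) / (1 + c(r − 1)). For r = 2:
- d = 5%, c = 5%: 2.05/1.05 = 1.95
- d = 10%, c = 5%: 2.10/1.05 = 2.00
- d = 10%, c = 2%: 2.10/1.02 = 2.06

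The result can lie below, at or above the true value.

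**6. Counting in both analyses.** With Cruïlla's follow-up taken from its last day, a dual attendee is a case in both only if positive on 11–17 July. A positive on 18–24 July counts for Cruïlla only.

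**The case against.** The effect is assumed rather than documented, and it is mostly small: at c = 3% a ratio of 2 becomes 1.94. Section 8.2 plans frequencies by group and names no risk ratio. The additional analysis in section 7.1 uses windows that do not overlap (step 3). A sensitivity analysis of dual attendees is something a statistical analysis plan could well contain, and that plan is not at hand.

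Much of this stands. The size is unknown, and the ratio is used here only to express it. The additional analysis may largely separate the festivals, provided its exclusions are applied to controls by their pair's date, which is not stated. It leaves the primary analysis unprotected. The control definition, however, is fixed in the protocol itself, so that part is not a detail left for later.

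A reader might also infer more than the documents support:
- *Both comparisons are equally blurred.* Step 3 shows that the Cruïlla comparison is only weakly affected.
- *The flaw hides transmission.* That considers only exposed controls; dual attendees act the other way in the CanetRock comparison.
- *Gate positives serve as their own festival's controls.* Sections 1.10, 6.1 and 8.1 put everyone screened at a festival in that festival's own population. The gap is only that one festival's gate positives could be drawn for the other.
- *Ticket returners enter the control cohorts.* Section 7.3 describes them only as a number, and they tested positive before the event, whereas the endpoint counts positives afterwards.
- *Dual attendees always count twice.* This holds only for the shared days. As the analyses are independent and the endpoint does not attribute the source of infection, it is not in itself an error.

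**Conclusion.** The point holds, chiefly for CanetRock. The stated control rule admits people exposed at a comparable screened festival on days 5 to 7 of CanetRock's 14-day follow-up, and the plan has no rule for CanetRock attendees who went on to Cruïlla. For Cruïlla the effect is weaker and runs through late-detected infections.

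Under an assumed true ratio of 2 and assumed exposed shares of 3% to 10%, exposed controls alone would lower the observed ratio to between 1.94 and 1.82. These figures assume that the other festival carries the same ratio and that its whole excess falls inside the follow-up. Once dual attendees are allowed for, the net direction for CanetRock cannot be stated. The distortion is probably small to moderate. It is worth preventing because it sits in the primary comparison and costs almost nothing to remove in advance.

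**What to change.** Add to section 6.4: controls for either festival must not appear in the Ag-RDT screening list of Cruïlla or of CanetRock; the health authority applies this before pairing. Sections 1.7 and 1.10 should be worded to match. The rule also removes one festival's gate positives from the other's control pool. It is feasible because sections 1.7 and 9.2 have both festivals' data going to the health authority. It needs to come before pairing because section 7.3 has control test results supplied in aggregate, so the research team may be unable to remove exposed controls afterwards.

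Flag attendees of both festivals and repeat each comparison without those pairs. The control exclusion alone would leave the second exposure on the attendee side (with r = 2 and d = 5%, at most 2.05 instead of 2), so this repeat makes the exclusion symmetric. If control results are supplied in aggregate, the authority would need to provide the counts with and without those pairs.

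No exclusion of ticket returners is proposed, since the documents show only a count of them. The cost is a negligible loss of potential controls and one extra analysis.

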### ***6.2 Observation period***

Data regarding the number of SARS-CoV-2 positive test results in each cohort will be collected considering 14 days before and 14 days after the festival (24th June - 24th July).

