## **7 VARIABLES AND MEASURE INSTRUMENTS. MEASUREMENTS DEFINITION AND DESCRIPTION**

### **7.1 Primary endpoint**

To study the prevalence of Covid-19 among those attending the festivals, the following endpoint will be analysed:

- Frequency of subjects attending to the Cruïlla festival who report a positive test on SARS-CoV-2 within the 14 days after the festival.
- Frequency of subjects attending to the CanetRock festival who report a positive test on SARS-CoV-2 within the 14 days after the festival.
- Frequency of subjects in each control cohort who report a positive test on SARS-CoV-2 within the 14 days after the festival.

Additional analysis will be performed excluding the following subjects, who will be considered as not infected during the festivals:

- Subjects who tested positive on SARS-CoV-2 6 days after their last day attending the festival.
- Subjects who tested positive within 2 days after attending the festival.

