### **7.3 Data collection**

Ag-RDT result, and demographics, of the attendees was collected by Cruïlla Festival and the CanetRock Festival, after the individuals agreed to data capture for epidemiological and research purposes.

Data regarding vaccination status, and positive SARS-Cov-2 test of the attendees at the festival and the control group will be collected from the Catalan Health Department registry.

In addition to the data about the subjects who attended the festival, the following data will be used for the study:

- Number of subjects that purchased an entrance, who tested positive for SARS-CoV-2 before the festivals and returned their entrance (without participating in the Ag-RDT screenings nor attending the festivals).
- Aggregated results of SARS-CoV-2 tests for the control cohort, for the complete cohort and subdivided according to their COVID-19 immunity status.

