### ***8.2 Statistical methods***

All variables will be described for the entire study sample and for each study group. To this end, the following analyses are foreseen:

- Continuous data will be described by their mean, median, standard deviation (SD), quartiles, minimum, and maximum.
- Categorical variables will be described by frequency and percentages (n, %).

Study endpoints will be analysed per groups and using frequencies, as described above in section 7.

No data imputation will be made. Only the subjects observed will be analysed and the number of missing data will be described in each analysis.

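### The main comparison is worded in subjects in 7.1 but in positive tests in 1.7 and 6.2, and 7.1 lets a repeat positive from a pre-festival infection count as a post-festival case

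*Protocol*

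**What the plan says.** The protocol words the outcome in two units.

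**Persons.**
- Section 1.7, second paragraph: "The study will compare the number of individuals who tested positive for Covid-19 in each cohort, before and after the festival".
- Section 7.1, for attendees: "Frequency of subjects attending to the Cruïlla festival who report a positive test on SARS-CoV-2 within the 14 days after the festival", with a matching bullet for CanetRock.
- Section 7.1, for controls: "Frequency of subjects in each control cohort who report a positive test on SARS-CoV-2 within the 14 days after the festival".
- Section 8.2 points back to these definitions: "Study endpoints will be analysed per groups and using frequencies, as described above in section 7".

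**Tests.**
- Section 1.7, third paragraph (the short account of the data flow), compares "the number of positive SARS-CoV-2 tests between attendees and" controls over the 14 days after the festival.
- Section 6.2: "Data regarding the number of SARS-CoV-2 positive test results in each cohort will be collected", for 14 days before and 14 days after.

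**Unit not stated.**
- Section 7.3 lists "Aggregated results of SARS-CoV-2 tests for the control cohort", for the whole cohort and by immunity status. It does not say whether the aggregate counts persons or tests.

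No section says how to treat a person with more than one positive test, either within one window or on both sides of the festival.

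**The concern.** Tests and subjects are different numerators. A person with a positive antigen test, a confirmatory PCR and one further positive contributes three tests but one subject. If the registry extract followed the wording of 1.7 or 6.2, the comparison would reflect how often cases are retested as well as how many people were infected. If the control data arrived only as aggregate test counts, the research team could not reduce them to persons afterwards.

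A second problem remains even when subjects are counted. Read literally, 7.1 asks only whether a subject has a positive test in the 14 days after the festival. Someone first positive shortly before it, with a repeat positive shortly after, meets that definition although the infection began earlier. The two cohorts are not equally exposed to this. Under 6.3, those exposed to a festival had a negative rapid antigen test at screening. Under 7.3, some ticket holders who tested positive beforehand returned their tickets without being screened. No comparable screen is stated for controls. Carried-over positives can therefore raise the control frequency more than the attendee frequency and make the festivals look safer.

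The rationale says the results are meant to inform on the effectiveness of the preventive measures for future events, so the direction of such an error matters.

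**Working it through.** The protocol states no rate, ratio or sample-size calculation, so there is no figure to reproduce. The check sets the passages side by side and sizes the possible distortion under stated assumptions.

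**1. Which unit governs.** Section 7.1 is the only endpoint definition. It uses subjects in every bullet, and 8.2 refers the analysis to section 7. On that reading, a person retested within the window counts once. The test wording in 1.7 and 6.2 conflicts with it, and 7.3 does not settle which unit the control aggregate uses.

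**2. Both cohorts counted in tests.** Assume equal true risk per person. Let rA and rC be the extra positive tests per case in attendees and controls. The documents give neither, so all values are assumptions. Pairing is 1:1, so the denominators cancel:

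ratio of test counts = (1 + rA) / (1 + rC)

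| rA | rC | Ratio (true value 1.00) |
|---|---|---|
| 0.1 | 0.1 | 1.1/1.1 = 1.00 |
| 0.3 | 0.3 | 1.3/1.3 = 1.00 |
| 0.2 | 0.1 | 1.2/1.1 = 1.09 |
| 0.3 | 0.1 | 1.3/1.1 = 1.18 |
| 0.5 | 0.1 | 1.5/1.1 = 1.36 |
| 0.1 | 0.3 | 1.1/1.3 = 0.85 |

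In counts, take 40000 persons per cohort (the number screened at Cruïlla; fewer will be analysed) and an assumed 1% risk. Each cohort then has 400 cases. With rA = 0.3 and rC = 0.1 these become 520 and 440 positive tests, and 520/440 = 1.18.

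Equal retesting inflates both counts but leaves the ratio at 1.00. Only unequal retesting distorts it, in either direction.

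**3. Subjects counted, with carry-over.** Let cA and cC be the carried-over cases per new case in the post-festival window. Literal 7.1 counting multiplies the ratio by (1 + cA) / (1 + cC). The limiting case is that the entry screen removes all carry-over in attendees (cA = 0). For assumed cC of 0.1, 0.2 and 0.3, the factor is then 1/1.1 = 0.91, 1/1.2 = 0.83 and 1/1.3 = 0.77. With cA = cC it is 1.00. These values only show direction and form; the protocol supplies no figure for either quantity.

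Two features could weaken the asymmetry. Pairing on immune status includes previous infection and may balance some recent infections, although no rule on their timing is stated. And 8.1 words the analysis set as everyone tested, so if screen-positive persons were kept on the attendee side, the direction in this step would no longer be assured.

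**4. After the fix.** If each person counts once, in the window holding the first positive of the episode, the factors in steps 2 and 3 are 1.00 whatever the retesting.

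**The case against.** The strongest reply is that the endpoint is already clear. Section 7.1 names subjects for attendees and controls, and 8.2 adopts it. The test wording in 1.7 sits in a summary of data flow, next to a sentence that speaks of individuals. Section 6.2 sets an observation period, and collecting test results is compatible with analysing persons. The aggregates in 7.3 could equally be persons positive and negative. Section 9.2 and its anonymization procedure describe records of attendees and controls merged through a subject code, so the registry can count persons. A detailed rule for repeat positives may sit in an analysis plan that is not shown.

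Most of this stands. It means multiple counting is not the planned analysis, and that the size of any distortion rests wholly on assumed rates.

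A reader might infer something stronger: that attendees will be counted as persons and controls as tests. That would multiply the ratio by 1/1.2 = 0.83 or 1/1.3 = 0.77 for 20% or 30% retesting, even with equal retesting. The documents do not support this. The control bullet of 7.1 requires subjects, 6.2 applies one unit to each cohort, and 9.2 describes person-level linkage for both.

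Two things survive the reply. The protocol does contradict itself on the unit of its main comparison, and the pointer in 8.2 to section 7 takes in 7.3, where the control unit is left open. And the carry-over problem does not depend on the test wording: it follows from the literal endpoint definition in 7.1.

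**Conclusion.** The inconsistency is real and should be removed before the registry extract is drawn. Section 7.1 should govern. Under it a person retested within the window counts once, so multiple counting arises only if the 1.7 or 6.2 wording is carried into the extract. Even then, with both cohorts in tests, the ratio changes only if retesting differs between them: roughly 0.85 to 1.36 over the assumed values, and 1.00 when it is equal.

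The carry-over point applies to the endpoint as written. Its likely direction favours the festivals, given the negative entry test for attendees and no stated screen for controls. Its size cannot be derived from the document.

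It would be wrong to conclude that the primary comparison has been shown to be biased. What is shown is conflicting wording, and an endpoint definition that admits repeat positives from earlier infections. Severity is minor to moderate, not a must-fix.

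**What to change.** - **1.7 and 6.2:** replace positive tests and positive test results with the number of subjects with at least one positive SARS-CoV-2 test.
- **7.1:** count each person once, in the window that contains the first positive of the episode, by the same rule in both cohorts. What separates one episode from the next can be left to the analysis plan. The rule also classifies a person with positives on, say, days 1 and 4 in the additional analysis, which is currently undefined.
- **7.3:** state that the control aggregates are persons with a first positive in the window over persons in the cohort, overall and by immunity status.

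The cost is wording in four sections and a de-duplication step at the registry, using the pseudonymised code that 9.2 already provides for. No new data source is needed: pairing on immune status already requires previous infections to be looked up for both cohorts.
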